### Procedure for unblinding if needed {17b}

Not applicable.

## Data collection and management

### Plans for assessment and collection of outcomes {18a} and data management {19}

Data will be collected in the following formats: paper, electronic survey database, and digital audio. All data will be coded with a unique numerical identifier. A list of names of the recruited participants and their corresponding numerical identifiers will be kept in a password-protected digital spreadsheet only accessible to project personnel named in this protocol. Electronic survey data will be kept in a Qualtrics account only accessible by the research team. No identifiable information will be collected in Qualtrics and responses will only be identified by a unique numerical identifier.

Other non-electronic identifying details (e.g. consent forms) will not be stored with research data. All paper notes will be kept for at least 5 years post any publication of results in a locked filing cabinet. Data will be shredded and disposed of securely after this time. Digital audio files will not contain any identifiable information about participants, for example, they will not be asked their name during the audio-recorded interview. Digital audio files will be labelled with participants’ unique numerical identifier and stored on a USB drive which will be locked in a filing cabinet. The password is available only to the research team. All files are protected using 128-bit encryption methods which are the gold standard in document protection. Passive data from the Peer Tree will also be collected. This information is collected and stored on secure online servers in line with Australian standards. This is part of the application development and it will not collect any information that can personally identify the participant.

### Plans to promote participant retention and complete follow-up {18b}

Participants in the intervention will be contacted weekly for the duration of the trial to promote engagement and retention through the intervention. Participants in control will be contacted 2 weeks before each assessment to schedule the next assessment. A reminder will be sent via text message a day prior to the assessment.

### Confidentiality {27}

All data will be stored with a unique numerical identifier rather than the participant’s name. All identifiable documents will be stored in a locked filing cabinet separate from assessment documents.

### Plans for collection, laboratory evaluation, and storage of biological specimens for genetic or molecular analysis in this trial/future use {33}

Not applicable. No biological specimens are being collected.

## Statistical methods

### Statistical methods for primary and secondary outcomes {20a}

All data processing and analysis will occur either in the statistical package for the Social Sciences (SPSS) or Mplus. Data manipulation will only occur if the data violates the statistical assumptions for the tests that we would be conducting. In this instance, the data will be transformed into a format that does not jeopardise the interpretability of the scores.

An intention-to-treat (ITT) analysis will also be conducted on all participants who were enrolled in the project but dropped out of the study. A mixed-model analysis will be used to determine whether a greater change in loneliness occurs over time for the Peer Tree group compared with the control group. This form of analysis creates an unbiased view of the intervention by including every participant who was assigned to each group in the final analysis, rather than those who contributed to each data point in the study. That is, if 15 people were assigned to an intervention but only nine of them completed the intervention, the ITT analysis would include all 15 participants in the analysis to provide an appropriate measure of what the effect would look like with every participant included.

A per-protocol analysis using mixed-model analysis of variance will be conducted to determine whether a change in loneliness occurs over time more so for the Peer Tree group compared with the control condition. Time (i.e. baseline, post-intervention, follow-up) will be the repeated measure factor, while intervention (i.e. Peer Tree vs control) will be the between-participant factor. Two-tailed Pearson’s *r* correlations will be calculated to assess the relationships between our primary outcome, loneliness, and secondary outcomes. This will be used to determine the suitability of conducting additional, regression-based analyses. In the instances that there are violations to the assumptions of these tests, we envisage that any combination of the following will be used to answer our focal questions: standard and hierarchical regression, mediation and multiple mediation, latent trajectory modelling, *t*-tests, and mean comparisons.

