##### Peer tree feasibility

Feasibility will be assessed by considering four key factors: uptake, attrition, retention, and application completion. Uptake is defined as the number of potentially eligible young people who attended the baseline assessment. We set an apriori threshold of at least 50% of people who were eligible would attend a baseline assessment. Attrition is defined as the number of participants who attended the baseline assessment but failed to log into the app for more than three consecutive days and where researchers were unable to contact the participant. We set a priori threshold of a 30% attrition rate. Retention is defined as the number of participants who complete the intervention. Application completion is defined as accessing and completing at least 50% of the app (21 out of 42 days) within the maximum allocated time of 8 weeks. These criteria are consistent with our previous pilot trials of +Connect [32, 33].

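### The intention-to-treat set is misstated as the dropouts, and neither the ITT nor the per-protocol analysis of loneliness is named as primary

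*Protocol article*

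**What the plan says.** Loneliness is a primary outcome (Outcomes {12}). It carries the main hypothesis, significantly lower loneliness than control (Objectives {7}), and the sample size (Sample size {14}).

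Statistical methods {20a} describes two analyses of it.

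- **ITT.** The population is introduced with "An intention-to-treat (ITT) analysis will also be conducted on all participants who were enrolled in the project but dropped out of the study". The model, which sets this group against control, is given as "A mixed-model analysis will be used to determine whether a greater change in loneliness occurs over time for the Peer Tree group". The paragraph then describes the approach as "including every participant who was assigned to each group in the final analysis, rather than those who contributed to each data point in the study". Its example supposes that "if 15 people were assigned to an intervention but only nine of them completed the intervention". The stated consequence for the analysis set is that "the ITT analysis would include all 15 participants in the analysis".
- **Per-protocol.** "A per-protocol analysis using mixed-model analysis of variance will be conducted to determine whether a change in loneliness occurs over time". The factors follow this sentence: "Time (i.e. baseline, post-intervention, follow-up) will be the repeated measure factor", with intervention as the between-participant factor.

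Neither analysis is called primary. Three other places bear on the point:

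- Peer tree feasibility: "Application completion is defined as accessing and completing at least 50% of the app", that is 21 of 42 days, within 8 weeks. Retention means completing the intervention. Attrition is defined by failure to log in combined with failed contact.
- Section {11b} leaves the use of data collected before withdrawal to a judgement of whether including them is sensible.
- Section {20c} relies on the ITT analysis, in place of imputation, for participants who withdraw.

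**The concern.** The sentence that defines the analysis population for a primary outcome contradicts the explanation that follows it. The ITT analysis also stands in for a missing-data method under {20c}, so the misstatement reaches further than one label.

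The ranking is open as well. ITT is something done in addition, and the per-protocol ANOVA answers the same question with its factors set out more fully. Once results are known, either could be presented as the efficacy finding. If the per-protocol result were used, and its set were built on the app-based criteria, low-engagement participants would be removed from Peer Tree while their counterparts stayed in control. The comparison would no longer be between randomised groups, and the likely direction of the error favours the app.

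**Working it through.** **1. The ITT set under the plan's own example.** Assigned 15, completed 9.

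- Explanation and example: 15 of 15 analysed.
- Literal opening sentence: at most 15 − 9 = 6 analysed. It is at most 6 because not completing the intervention is not the same as leaving the study.

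Both cannot define the ITT set.

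**2. Who can fail the adherence criteria.** Completion and retention require the app or the intervention, and attrition requires not logging in. Controls receive no app, so they cannot fail the completion criterion. Withdrawal and repeated failed contact ({11b}) can occur in either arm.

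**3. Size of a one-arm selection (illustration).**

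Inputs:
- 42 participants at 1:1, so 21 per arm.
- Exclusion of 30% (the plan's attrition threshold) or 40% (6/15 in its ITT example). Neither is a forecast.
- Correlation r between completion and better outcome of 0, 0.2, 0.3 or 0.5. This is an assumption; the protocol gives no figure.
- No true effect, SD 1.

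If a proportion p of one arm is kept by a threshold on a normal trait correlated r with outcome, the expected bias is r × φ(z)/p, where z is the threshold.

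- p = 0.60: z = −0.253, φ(z)/p = 0.644. Bias for r = 0.2, 0.3, 0.5 is 0.129, 0.193, 0.322 SD.
- p = 0.70: z = −0.524, φ(z)/p = 0.348/0.70 = 0.497. Bias is 0.099, 0.149, 0.248 SD.

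A simulation of 4,000 trials per setting, with a two-sample t-test on one endpoint and all 21 controls kept, gives the following. Negative means lower loneliness in Peer Tree.

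| Excluded from Peer Tree | r | Bias (SD) | Type I error |
|---|---|---|---|
| 30% (15 vs 21) | 0 | 0.00 | 4.5% |
| 30% | 0.2 | −0.09 | 6.2% |
| 30% | 0.3 | −0.14 | 7.0% |
| 30% | 0.5 | −0.23 | 10.6% |
| 40% (13 vs 21) | 0 | 0.00 | 5.0% |
| 40% | 0.2 | −0.11 | 5.8% |
| 40% | 0.3 | −0.19 | 9.2% |
| 40% | 0.5 | −0.29 | 13.1% |

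The simulation standard error of a rejection rate is √(p(1−p)/4000), about 0.3 to 0.5 percentage points, so the two rows at r = 0.2 do not differ. Analysing all 21 per arm gave bias within 0.005 SD of zero and type I error of 4.2–5.3%. Applying the same selection to both arms gave bias within 0.008 SD of zero. In this model the bias therefore comes from the asymmetry.

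**The case against.** The strongest reply is that the opening ITT sentence is a drafting slip, probably meant to say that dropouts are included. The same paragraph puts this right, the example analyses everyone, and the text presents ITT as the unbiased view. The trial is a 42-person pilot, and membership of a per-protocol set is commonly left to an analysis plan that is not shown.

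Much of that stands. The missing per-protocol definition is not the point here, and several stronger readings that a reader might infer are not supported:

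- *That an analysis of dropouts alone is planned, on about 13 people (30% of 42 = 12.6).* Nothing else in the protocol plans this. Attrition is also defined by app log-in; applied to the 21 in Peer Tree it gives 0.30 × 21 = 6.3.
- *That the only loneliness model is the per-protocol ANOVA.* The ITT paragraph also names a mixed-model analysis of change by group. The ANOVA is only the more fully described of the two.
- *That per-protocol exclusions can fall only on Peer Tree.* No per-protocol rule is stated, the 21-of-42 threshold is a feasibility measure never tied to that analysis, and controls can be lost through withdrawal, failed contact or missed assessments.
- *That the ANOVA discards anyone who misses a visit.* No deletion rule is given.
- *That the bias is a known share of the planned effect.* The protocol says only that the effect is moderate and gives no number.

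What the reply does not remove is the contradiction in the stated population or the lack of a named primary analysis. The article addresses both matters itself, so they are not details deferred elsewhere.

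**Conclusion.** The point holds on the text. The ITT population is stated wrongly and contradicts its own explanation (at most 6 of 15 against 15 of 15). Two analyses of one primary outcome are also left unranked.

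The bias is conditional. It arises only if the per-protocol result carries the efficacy conclusion, its set is built on the app-based criteria, and completion is related to outcome. Under those conditions, 30–40% exclusion and an assumed correlation of 0.2–0.5 give about 0.1–0.3 SD and type I error of about 6–13%. The figures come from a single-endpoint comparison rather than the repeated-measures model, so they indicate scale only.

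**What to change.** Replace the opening ITT sentence in {20a} with: *The primary loneliness analysis is ITT: all randomised participants, in the arm allocated, regardless of app use or completion, using a likelihood-based mixed model (time, group, time × group) with every available UCLA-LS3 score.* Because baseline is a level of time, a participant with only a baseline score still enters the model.

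Add that the per-protocol analysis is supportive only and is not a basis for the efficacy conclusion. If it is kept, state its set for both arms.

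Reconcile {11b} with this by including all data collected before withdrawal, without the discretionary clause.

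The cost is a few sentences, with the same data and software. The headline estimate may be smaller than the per-protocol one. The likelihood-based model still assumes that scores are missing at random, and the text should say so. The change should be made before loneliness is compared by arm.

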## Objectives {7}

The objective of this study is to evaluate the acceptability, feasibility, safety, and initial efficacy of a positive psychology smartphone application intervention called Peer Tree. Peer Tree is a digital smartphone intervention targeting loneliness and is a new iteration of our previous application +Connect. Peer Tree includes many features from +Connect [30, 31] but also includes the personalisation of modules based on user symptom profiles, a peer- and clinician-moderated chat forum, and animated videos to address loneliness in young people using a positive psychology framework.

It is hypothesised that Peer Tree participants, compared with the control participants, will report significantly lower loneliness at post-intervention, and these effects will remain at follow-up. It is also anticipated that Peer Tree participants, compared with control participants, will report significantly lower social anxiety and depressive symptoms, and higher quality of life and well-being outcomes at post-intervention as well as at follow-up.

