### Sample size {14}

A power analysis was conducted using G*Power 2.0 software. The *F* statistic function for an intervention design was used to obtain the relevant sample size. This is established using loneliness outcome data and is estimated using the effects sizes derived from +Connect. Loneliness was used to determine statistical power as it was the target variable of our primary outcomes. This revealed that 42 participants are needed to detect a moderate effect with 80% power.

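### The stated loneliness test (change over time by arm) cannot show the hypothesised post-intervention effect or its persistence; name the visit contrasts instead

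*Protocol article*

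**What the plan says.** Objectives {7} of the protocol article gives a hypothesis tied to visits: compared with control, Peer Tree participants "will report significantly lower loneliness at post-intervention, and these effects will remain at follow-up". That is one arm difference at each of two visits.

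Statistical methods for primary and secondary outcomes {20a} describes the ITT test this way: "A mixed-model analysis will be used to determine whether a greater change in loneliness occurs over time for the Peer Tree group", with control as the comparison. It does not list the visits. The next paragraph, on the per-protocol mixed-model ANOVA, asks the same question and gives the factors: "Time (i.e. baseline, post-intervention, follow-up) will be the repeated measure factor", "while intervention (i.e. Peer Tree vs control) will be the between-participant factor". The same section mentions t-tests and mean comparisons only as options if test assumptions are violated. No arm difference at a named visit is given as the deciding test.

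Sample size {14} is built on loneliness. It says an *F* "statistic function for an intervention design was used to obtain the relevant sample size", and concludes: "This revealed that 42 participants are needed to detect a moderate effect with 80% power".

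**The concern.** With two arms and three visits, a test of whether change over time differs by arm is an arm-by-time interaction with 2 degrees of freedom. Its null hypothesis is that the two arms have parallel profiles over all three visits. It can be rejected because the arms differ at both later visits, because they differ only at follow-up, or because they differ at post-intervention and have converged again by follow-up. Only the first of these is the pattern that Objectives {7} predicts.

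A significant result could therefore be reported as support for the hypothesis when there was no post-intervention effect, or when the effect had gone three months later. Loneliness is listed as a primary outcome in Outcomes {12}, and the sample size rests on it, so this is the result readers will look at first.

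**Working it through.** **Inputs from the protocol.** N = 42 with 1:1 allocation, so n = 21 per arm; three visits; two arms; 80% power for a moderate effect.

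**Assumptions, because the protocol gives no figure.** Two-sided alpha 0.05; equal correlation rho between visits, 0.5 to 0.8; effect d of 0.5 or 0.8 SD; no dropout.

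**1. The plan's own figure.** N = 42 cannot be reproduced from what is stated, because the effect size, alpha, correlation and number of measurements are missing. Effect sizes are said only to be "estimated using the effects sizes derived from +Connect". The interaction test has noncentrality lambda = f² × N × m / (1 − rho). With f = 0.25, m = 3 and rho = 0.5, it needs N = 28. With f = 0.20, lambda = 0.04 × 42 × 3 / 0.5 = 10.08 and power at N = 42 is 80.3%. So 42 fits a three-visit interaction under one set of assumptions, but other sets fit too (for example two visits, f = 0.20, rho = 0.6: 80.7%).

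**2. What the interaction can tell apart.** Write the arm difference at baseline, post-intervention and follow-up as a pattern. Then lambda = (n/2) × S / (1 − rho), where S is the sum of squared deviations of the pattern from its own mean.

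- Sustained (0, d, d): deviations −2d/3, d/3, d/3, so S = 2d²/3
- Follow-up only (0, 0, d): deviations −d/3, −d/3, 2d/3, so S = 2d²/3
- Transient (0, d, 0): deviations −d/3, 2d/3, −d/3, so S = 2d²/3

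All three give lambda = 7d² / (1 − rho), so the test rejects equally often whichever is true. At rho = 0.5:

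- d = 0.5: lambda = 3.50, rejection 36%
- d = 0.8: lambda = 8.96, rejection 75%

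At rho = 0.7 and d = 0.5, lambda = 5.83 and rejection is 55%. With a follow-up-only effect, a baseline-adjusted comparison at post-intervention rejects in 5%, as it should. The percentages depend on d and rho; their equality across the three patterns does not.

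**3. If time were fitted as a straight line.** At rho = 0.5 and d = 0.5, sustained and follow-up-only effects each reject in 35%, and a transient effect in 5%. A zero post-intervention effect is still not told apart from a sustained one.

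**4. Power for a sustained 0.5 SD effect.** The baseline-adjusted post-intervention difference has noncentrality d / √[(1 − rho²) × 2/n]. At rho = 0.5 this is 0.5 / √(0.75 × 2/21) = 1.87, giving 45%. Simulation, which allows for chance baseline imbalance, gives about 44%. In the table the interaction column is from the formula and the other two are from simulation.

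| rho | Interaction | Adjusted post-intervention | Post-intervention and follow-up both significant |
|---|---|---|---|
| 0.5 | 36% | 44% | about 25% |
| 0.7 | 55% | 58–59% | about 42% |
| 0.8 | 74% | 74% | not needed here |

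Simulated values carry an error of a point or so; in the simulations the interaction came out at 36–37% and 55–56% in the first two rows.

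**The case against.** **The ITT sentence does not fix an omnibus test.** It names no visits, no degrees of freedom and no role for baseline, and it is worded directionally. A mixed model can supply visit contrasts, and in randomised arms greater change from baseline to post-intervention addresses the same effect as a lower score there. A separate analysis plan may name that contrast. This stands in part: the 2-df reading is explicit only for the per-protocol analysis. But both paragraphs ask the same question, neither names a visit, and visit-level comparisons appear only as a fallback. The article states a test, and that test does not answer its own hypothesis.

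**The plan wastes power.** A reader might infer that the interaction is clearly weaker against a sustained effect. The figures do not support that as a general statement. Against the adjusted post-intervention contrast, the loss is about 8 points at rho = 0.5, about 3 at 0.7 and none at 0.8. Against an unadjusted change to post-intervention (35% at rho = 0.5) there is no loss. A baseline-adjusted mean of both later visits would reach 61% at rho = 0.5, but it does not test the two-part hypothesis either and is not proposed here.

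**Baseline is used inefficiently.** A reader might also infer that listing baseline as a level of time reduces it to a change score. The article does not settle this for the ITT model; a model with a common baseline mean recovers essentially the efficiency of covariate adjustment.

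**This is a pilot, and an arm-by-time model is conventional there.** True, but Objectives {7} predicts significance and Sample size {14} claims 80% power, so the test should match the claim.

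**Conclusion.** The mismatch between hypothesis and test is in the text and should be corrected. Read as the arm-by-time interaction, the stated test has the same chance of rejecting for sustained, follow-up-only and transient effects of equal size (about 36% at 0.5 SD and 75% at 0.8 SD with rho = 0.5). A significant result therefore does not show an effect at post-intervention or that it lasts.

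That conclusion rests on the algebra for three equally correlated visits. The percentages also rest on assumed effect size, correlation and alpha and on full retention, so they show rough size and are not estimates of this trial's power. The case for change is the meaning of the result; the power gain is modest at best.

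**What to change.** State in {20a} that the loneliness hypothesis is tested by the ITT mixed-model arm difference in UCLA-LS3 at post-intervention, adjusted for baseline UCLA-LS3, either as a covariate or through a common baseline mean. Test the arm difference at follow-up second, and only if the first is significant. Base any statement that the effect lasts on that second contrast and its 95% confidence interval. Report the overall arm-by-time interaction as descriptive.

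The change uses the same data, visits and software, so it costs wording only. The one downside is that claiming both parts needs both contrasts to be significant. For a sustained 0.5 SD effect that happens in about 25% of trials at rho = 0.5 and about 42% at rho = 0.7, less often than a significant interaction (36% and 55%). The order still allows the post-intervention part to be claimed alone.

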**Methods:**

This will be a pilot randomised controlled trial (RCT) comparing a strength-based digital smartphone application (Peer Tree) with a control condition. Forty-two young people enrolled at university will be recruited for this pilot RCT. Participants with suicidal ideation or behaviours, acute psychiatric symptoms in the past month, or a current diagnosis of a mood or social anxiety disorder will be excluded. Allocation will be made on a 1:1 ratio and will occur after the initial baseline assessment. Assessments are completed at baseline, at post-intervention, and at follow-up. Participants in the control condition complete the same three assessment sessions. The primary outcome of the study will be loneliness. Depression, social anxiety, quality of life, acceptability, usability, feasibility, and safety of Peer Tree will also be measured as secondary outcomes.

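### The stated loneliness model leaves the arm means free to differ at baseline, so its change-from-baseline contrast is valid but less precise than one that uses randomisation at baseline

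*Protocol article*

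**What the plan says.** All analysis wording is in the Protocol article, section {20a}.

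- **ITT analysis.** "A mixed-model analysis will be used to determine whether a greater change in loneliness occurs over time for the Peer Tree group" relative to control. The paragraph says that all assigned participants are to be analysed. It lists no time levels, mean structure or covariates.
- **Per-protocol analysis.** A mixed-model ANOVA in which "Time (i.e. baseline, post-intervention, follow-up) will be the repeated measure factor", "while intervention (i.e. Peer Tree vs control) will be the between-participant factor". Baseline loneliness is therefore one of three outcome levels, and no common baseline mean is imposed.

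Elsewhere in the article:

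- The abstract's Methods state: "Allocation will be made on a 1:1 ratio and will occur after the initial baseline assessment". Section {16a} describes blocked randomisation and mentions no stratification by loneliness.
- Table 1 schedules the UCLA-LS3 at all three visits.
- The Covariates heading under Outcomes {12} covers the IIP-32 and a COVID-19 item. It does not list baseline loneliness and does not tie either measure to a model.
- Objectives {7} frames the hypothesis as a difference between arms in the level of loneliness at post-intervention, maintained at follow-up.

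**The concern.** Allocation is random and follows the baseline assessment, so the true mean loneliness of the two randomised arms is equal at baseline. A model with a free arm mean at every visit estimates that difference instead of using the known value of zero. With complete data, its contrast between baseline and a later visit is then a difference in raw change scores.

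Two things follow. The contrast has more sampling variance than one that adjusts for baseline. And when the arms differ at baseline by chance, subtracting the whole difference over-corrects, because part of it would have disappeared by regression to the mean. In a trial of 42 that tests a superiority hypothesis on loneliness, the baseline score is already collected and could do more work.

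**Working it through.** **Inputs from the protocol.** N = 42 at 1:1, so 21 per arm; three visits; two arms.

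**Assumed, because the protocol does not give them.** Two-sided alpha 0.05; a true difference of 0.5 SD; equal variance (1 SD²) at each visit; baseline-to-post correlation r of 0.5 to 0.8.

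**1. The plan's own figure.** Section {14} says "The *F* statistic function for an intervention design was used to obtain the relevant sample size", with the effect "estimated using the effects sizes derived from +Connect", and concludes "42 participants are needed to detect a moderate effect with 80% power". It gives no effect size, alpha, correlation or number of measurements, so 42 cannot be derived from the stated inputs alone. The noncentral F for the arm-by-time interaction has λ = N·f²·m/(1−ρ), with (m−1) and (N−2)(m−1) degrees of freedom. For f = 0.20, m = 3, ρ = 0.5: λ = 42 × 0.04 × 3/0.5 = 10.08, power 0.803, so N = 42 is reached. With f = 0.25 and the same m and ρ, 28 would suffice. So 42 is compatible with sizing on the interaction, but the protocol does not confirm it.

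**2. Precision at one post-baseline visit.** Variance per participant:

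- change score: 2(1−r)
- baseline-adjusted: 1−r²
- ratio adjusted/change: (1−r²)/[2(1−r)] = (1+r)/2

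The standard error of the arm difference is √(variance × 2/21). Power is from the noncentral t, with 40 df (change) and 39 df (adjusted).

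| r | change variance | adjusted variance | ratio | power, change | power, adjusted | 95% CI half-width, change to adjusted |
|---|---|---|---|---|---|---|
| 0.5 | 1.00 | 0.75 | 0.75 | 35% | 45% | 0.62 to 0.54 SD |
| 0.6 | 0.80 | 0.64 | 0.80 | 42% | 51% | 0.56 to 0.50 SD |
| 0.7 | 0.60 | 0.51 | 0.85 | 53% | 60% | 0.48 to 0.45 SD |
| 0.8 | 0.40 | 0.36 | 0.90 | 70% | 75% | 0.39 to 0.38 SD |

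In sample-size terms, an adjusted analysis of 42 × 0.75 = 31.5, about 32 participants, matches the change contrast with 42 at r = 0.5. At r = 0.8 the figure is 42 × 0.90 = 37.8, about 38. Below r = 0.5 the loss is larger: at r = 0.3 the ratio is 0.65.

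**3. Chance imbalance.** The standard error of the baseline difference is √(2/21) = 0.31 SD. The chance of an absolute difference above 0.3 SD is 33%, and above 0.5 SD about 11%. Given an imbalance b (Peer Tree minus control), the change contrast is shifted by −(1−r)·b. For b = 0.3 SD the size is 0.15 SD (r = 0.5), 0.09 SD (0.7) or 0.06 SD (0.8), which is 30%, 18% or 12% of a 0.5 SD effect. If Peer Tree happens to start lonelier, its benefit is overstated; if less lonely, understated.

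**4. Simulation.** 20,000 trials were run with 21 per arm, complete data, equal correlation between visits and a 0.5 SD effect at both later visits. Both estimators averaged −0.50 SD, so neither is biased.

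| r | variance ratio, change/adjusted | slope on imbalance, change | slope on imbalance, adjusted | power, 2-df interaction | power, adjusted post-intervention test |
|---|---|---|---|---|---|
| 0.5 | 1.30 | −0.50 | about 0 | 0.36 | 0.44 |
| 0.7 | 1.13 | −0.29 | about 0 | 0.55 | 0.59 |

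The variance ratios are slightly below the theoretical 1.33 and 1.18 because the simulation pays for estimating the slope.

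**The case against.** **The detailed factor structure belongs to the per-protocol analysis.** This is right. The ITT paragraph fixes only the target, "whether a greater change in loneliness occurs over time for the Peer Tree group compared with the control group", and a model with a common baseline mean could also answer that. A reader might infer that the protocol rules out baseline adjustment in the ITT analysis. It does not: it states none, and its wording matches the per-protocol comparison. An analysis plan that is not shown could supply the detail for ITT, but it would have to replace the stated structure for per-protocol.

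**The analysis is standard and valid.** This also stands. A reader might infer systematic bias, or that the whole baseline imbalance remains in the estimate. Neither is so. The contrast is unbiased over randomisations, and only the fraction (1−r) remains, with its sign reversed, conditional on the imbalance that occurred.

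**It is not always a single change score.** Correct. With three levels the default interaction test has 2 df, a post-intervention versus follow-up contrast does not involve baseline, and with missing visits a likelihood model is not a simple difference of raw changes. The simulated comparison with the 2-df test still shows a gain, but a modest one.

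**The size rests on undocumented inputs.** True. At r = 0.8 the gain is about five percentage points of power. The power levels above belong to an assumed 0.5 SD and do not contradict the protocol's 80%, which refers to a moderate effect without a number.

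**The Covariates heading suggests that some adjustment is foreseen.** Possibly, but it names other measures and no model.

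**Conclusion.** The point holds as a matter of efficiency. As stated, the per-protocol model leaves baseline arm means free, and the ITT model is described as the same comparison with no baseline adjustment. The arm-by-time contrast against baseline is valid. However, relative to a baseline-adjusted contrast it carries 1/0.90 = 1.11 to 1/0.75 = 1.33 times the variance for r from 0.8 to 0.5, and it retains a conditional shift of (1−r) times any chance imbalance.

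The direction of the precision loss holds for any r below 1, apart from the small cost of estimating a slope. Its size depends on r, which the protocol does not give, and the power figures also depend on the assumed 0.5 SD and on complete data. The plan should be changed because the gain is nearly free in a trial of 42. The present analysis would not be invalid without the change.

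**What to change.** In section {20a}, for both the ITT and per-protocol analyses, specify a likelihood-based mixed model that keeps all three visits, constrains the two arm means to be equal at baseline, and reports the arm contrasts at post-intervention and follow-up. This form keeps every randomised participant with a baseline score, in line with the section's ITT intention.

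Baseline UCLA-LS3 as a covariate, with its interaction with time and only the two later visits as outcomes, is an alternative where post-baseline data are present. It is not interchangeable when data are missing: it drops anyone with no later score, which matters when the feasibility section allows a 30% attrition threshold. In the per-protocol set, the equal-baseline constraint also assumes that exclusion is unrelated to baseline loneliness, an assumption the covariate form does not need.

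Apply the same approach to each secondary scale measured after baseline. This excludes the WHO QOL-Bréf, which Table 1 schedules at baseline only. If the IIP-32 or the COVID-19 item enters a model as a covariate, use its baseline value only.

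The cost is one sentence of analysis wording and at most one or two degrees of freedom. No new data are needed.
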